## Abstract

**Background:**

Brain inflammation plays a key role in ischemia/reperfusion (I/R) injury and is the main cause of “ineffective or futile recanalization” after successful mechanical thrombectomy (MT) in acute ischemic stroke (AIS). One of the primary sources of inflammatory cells after AIS are derived from the spleen. As an innovative and potential neuroprotective strategy after stroke, Remote Administration of Hypothermia (RAH) temporarily suppresses immune activities in the spleen, reduces the release of inflammatory cells and cytokines into blood, and thus reversibly diminishes inflammatory injury in the brain.

**Methods:**

This single-center, prospective, randomized controlled study (RCT) is proposed for AIS patients with anterior circulation large vessel occlusion (LVO). Subjects will be randomly assigned to either the control or intervention groups in a 1:1 ratio (*n* = 40). Participants allocated to the intervention group will receive RAH on the abdomen above the spleen prior to recanalization until 6 h after thrombectomy. All enrolled patients will receive standard stroke Guideline care. The main adverse events associated with RAH are focal cold intolerance and abdominal pain. The primary outcome will assess safety as it pertains to RAH application. The secondary outcomes include the efficacy of RAH on spleen, determined by spleen volumes, blood inflammatory factor (cells and cytokines), and on brain injury, determined by infarction volumes and poststroke functional outcomes.

**Discussion:**

This study aims to examine the safety and preliminary effectiveness of RAH over the spleen during endovascular therapy in AIS patients. The results of this study are expected to facilitate larger randomized clinical trials and hopefully prove RAH administration confers adjuvant neuroprotective properties in AIS treated with MT.

**Clinical trial registration:**

https://www.chictr.org.cn/. Identifier ChiCTR 2300077052.

## Introduction

1

Mechanical thrombectomy (MT) is recommended for acute ischemic stroke (AIS) patients with large vessel occlusion (LVO) due to high revascularization rates. However, almost half of the stroke patients who undergo successful revascularization still experience severe disability or death. This phenomenon has been known as “ineffective or futile recanalization” (1–3). It is crucial to develop neuroprotection strategies to protect the brain in addition to endovascular therapy.

An increasing number of studies have demonstrated that splenic-derived inflammatory cells are an important source of inflammatory infiltration within brain tissue and that post-stroke activation of splenic inflammatory cells invade brain tissue, exacerbating the inflammatory and thus ischemia/reperfusion(I/R) injury (4–7). It was reported that splenic contraction occurs in some stroke patients within 24–48 h, followed by gradual recovery of splenic volume with clinical function improvement, according to clinical studies (8). Animal experiments further confirmed a significant reduction in spleen volume during the acute phase of stroke and the transit of splenocytes from the spleen to the ischemic area in the brain (8, 9). These studies suggested that activation and release of splenic inflammatory cells were the key factor in exacerbating cerebral ischemia/reperfusion injury. Inhibition of the reaction may block the inflammatory cascade response in the brain, leading to neuroprotection. Because of the detrimental effects of splenic inflammatory cells and factors, splenectomy is a widely studied means of splenic suppression. Splenectomy in a mouse model resulted in lower blood levels of multiple inflammatory factors than normal mice (9), reducing inflammatory cell infiltration in the brain and reducing brain infarct volume (10). Splenic pulse treatment suppressed the immune response in septic rats (11), and splenic irradiation similarly reduced infarct volume in mice (12). However, these approaches are largely prohibited in clinical practice since they cause irreversible suppression of the spleen (10, 13, 14). In the current study, the RAH above the spleen is hypothesized to prevent splenic contraction and reduce the release of splenic inflammatory cells and cytokines, which in turn may decrease brain infarct volume and improve long-term neurological function after stroke in humans. Furthermore, before this proposed clinical trial, our team investigated the efficacy of Remote Administration of Hypothermia (RAH) to the spleen in animal models of middle cerebral artery occlusion. During the experiment, the spleen temperature was reduced to 27°C, leading to reduced brain inflammatory response, decreased infarct volume, and improved functional prognosis (unpublished data). While our original pre-clinical animal data remains unpublished, the connection between splenic response and stroke injury, as well as protective effects, has been discussed in a recent study. In this study, it was demonstrated that diminished splenic response through inactivation or knockout of GPR55 improved neurological outcomes in a rodent model (15).

## Methods and analysis

2

### Study design

2.1

This is a single-center prospective randomized controlled trial of AIS patients with LVO in the anterior circulation. We will determine the safety and preliminary efficacy of RAH in AIS patients with LVO in the anterior circulation with concurrent recanalization by MT. All participants or proxies will be informed of the potential risks and possible benefits and consent to participate in this study. This study was approved by the regional ethics committee and registered at www.chictr.org.cn (ChiCTR 2300077052).

Participants assigned to the intervention group will receive RAH prior to recanalization until 6 h after thrombectomy. All participants from either group will be given concurrent standard-of-care therapies consistent with the Guidelines for Stroke Management.

### Participants and screening

2.2

Participants will be recruited from the Stroke Intervention & Translational Center (SITC) in Beijing Luhe Hospital, Capital Medical University. Eligible patients will be randomly assigned to RAH or control group when they fulfill the inclusion criteria but not the exclusion criteria. The flowchart of the study is in Figure 1.

**Figure 1 fig1:**
[figure not shown]
Flowchart of the study.

The criteria for recruitment are as follows: (1) Age of 18–80 years; (2) Patients with AIS; (3) LVO of the anterior circulation confirmed by computer tomography angiography (CTA), magnetic resonance angiography (MRI), or digital subtraction angiography (DSA); (4) Baseline National Institute of Health stroke scale (NIHSS) score ≥ 6 and Alberta Stroke Program Early CT Score (ASPECTS) >5; (5) Less than 24 h from stroke onset; (6) Acute occlusion of intracranial or extracranial segments of the anterior circulation vessels (thrombolysis in cerebral infarction score [TICI] classification 0-I); and (7) Informed consent of the participant or legally authorized representative (in cases where the patient’s decision-making ability is impaired due to a stroke) will be obtained.

The criteria for exclusion are as follows: (1) Spontaneous revascularization or rapid spontaneous improvement in neurological function (NIHSS<6 points); (2) Unsuccessful revascularization with MT (TICI = 0); (3) Rapid improvement in symptoms after revascularization; (4) Cranial imaging showing infarct area exceeding one-third of the area supplied by the middle cerebral artery pre-MT; (5) Pre-stroke modified Rankin Scale (mRS) >2; (6) Blood glucose <2.7 or > 22.2 mmol/L; (7) Laboratory evidence of coagulation dysfunction (platelet count <40 × 10^9^/L, APTT >50 s, or INR >3.0); (8) Pregnancy; (9) Splenic-related hematologic disorders, hypersplenism, or suppression; (10) Hypersensitivity of the skin, such as cold urticaria; (11) Obesity of patients (BMI ≥28/waist circumference > 90 cm); (12) Abdominal injury, surgical trauma and other factors intolerance to splenic hypothermia; (13) Patients enrolled within 3 months prior to this clinical trial or already enrolled in another clinical trial; (14) Failure to obtain informed consent; and (15) Patients with Splenectomy.

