### Adjuvant neuroprotective strategy with RAH in addition to recanalization

3.4

As research progresses, the integration of neuroprotective measures with thrombolysis or thrombectomy is increasingly perceived as a pivotal step toward evolving comprehensive neuroprotective strategies for AIS (39, 40). Recent strides in MT for AIS have unveiled opportunities to effectively utilize additional neuroprotective treatments post-reperfusion (24, 41). Notable approaches include NA1 [an inhibitor of the excitotoxic post-synaptic density protein 95 (PSD-95)] (42), intra-arterial cooling infusion (37), and high-flow normobaric oxygen (NBO) (43). Drawing information from the neuroprotective influence of RAH over the spleen as observed in ischemic stroke animal models (submitted, unpublished data), our team would like to pioneer a clinically practical RAH methodology. This technique is geared toward establishing RAH’s neuroprotective effectiveness in AIS patients following endovascular recanalization. Our approach synergistically combines reperfusion and neuroprotection strategies, including recanalization therapy, hypothermia, and splenic inflammation inhibition. The goal is to mitigate I/R injuries and strengthen neurological function. We postulate that the combined regimen of RAH and MT might improve endovascular treatment outcomes more than MT alone. Such a combination could potentially enhance the functional outlook for AIS patients and diminish complications, including bleeding, disability, and mortality, especially in severe acute cerebral infarction cases. This comprehensive approach provides an optimized treatment model while also promoting healthcare efficiency and cost savings. By potentially reducing unnecessary medical costs, especially when using cost-effective methods like ice packs, it aligns with the broader goal of economical healthcare. Our method of regional cooling is not only user-friendly and effective but also versatile, hinting at its potential use in hypothermic treatments for different diseases and targeted organ therapies.

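### The TICI cut-off for an occluded vessel at entry (0-I) does not match the cut-off for failed thrombectomy (0 only), so a patient ending at TICI I counts as neither excluded nor clearly recanalised

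*Protocol article*

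**What the plan says.** Both cut-offs stand in section 2.2 of the protocol article. Inclusion criterion 6 requires "Acute occlusion of intracranial or extracranial segments of the anterior circulation vessels (thrombolysis in cerebral infarction score [TICI] classification 0-I". Exclusion criterion 2 is "Unsuccessful revascularization with MT (TICI = 0". The only other exclusion that depends on the course after the procedure is criterion 3, "Rapid improvement in symptoms after revascularization", which concerns clinical improvement and not the TICI grade.

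The population of interest is described in terms of recanalisation. The Abstract says that brain inflammation "is the main cause of “ineffective or futile recanalization” after successful mechanical thrombectomy (MT) in acute ischemic stroke (AIS". Section 2.1 sets the objective in "AIS patients with LVO in the anterior circulation with concurrent recanalization by MT". Section 3.4 states the efficacy aim: "This technique is geared toward establishing RAH’s neuroprotective effectiveness in AIS patients following endovascular recanalization".

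Under section 2.3 patients consent and are then randomised. Under section 2.4 cooling begins before recanalisation and continues until 6 hours after thrombectomy. Section 2.6 plans 20 patients per group.

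**The concern.** The same grade is read in two ways. Before the procedure, TICI I means that the vessel is occluded. After the procedure, TICI I is not a failure. A patient who enters at I and leaves at I has not changed grade, yet passes the rule meant to set aside failed procedures. So does a patient who moves from 0 to I.

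This matters because recanalisation defines the population in which the trial hopes to show an effect. In a patient whose vessel is still at a grade the protocol calls occluded, infarct volume and 90-day mRS may reflect the persisting occlusion more than any reperfusion injury that cooling could modify. Such patients lie outside the stated objective, and they could blur a preliminary efficacy estimate that the Abstract and Conclusion expect to inform later trials.

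**Working it through.** No figure in the article needs to be reproduced here. The sample size rests on rules of thumb for pilot studies, and its only arithmetic, 2 × 20 = 40, agrees with the stated total. The check is a comparison of definitions, followed by an illustration of size.

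**Step 1. Compare the cut-offs (section 2.2).**
- Occluded at entry (inclusion 6): {0, I}.
- Unsuccessful after thrombectomy (exclusion 2): {0}.
- Difference: {I}.

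| Grade at entry | Grade after MT | Occluded by the entry rule? | Removed by exclusion 2? |
|---|---|---|---|
| 0 or I | 0 | Yes | Yes |
| 0 | I | Yes | No |
| I | I | Yes | No |
| 0 or I | above I | No | No |

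The second and third rows are the gap.

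**Step 2. Look for another rule that closes it.** Exclusion 3 removes only rapid improvers. The remaining exclusions concern status before or independent of the procedure. None removes a patient on the ground of a final TICI I.

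**Step 3. Place the final grade in time.** Randomisation precedes the intervention (section 2.3), and cooling starts before recanalisation (section 2.4). Final TICI is therefore known only after allocation, and exclusion 2, as worded, acts on randomised patients.

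**Step 4. Size, on an assumption.** The article gives no frequency of final TICI I. Let p be the share, assumed to lie between 0% and 10%.
- Patients affected: p × 40 = 0 to 4 in total, or p × 20 = 0 to 2 per arm if evenly spread.
- If these patients had none of a reperfusion-related benefit D and the others had all of it, the average benefit would be (1 − p) × D, a loss of 0% to 10% of D.
- One patient in an arm of 20 is 1/20 = 5 percentage points of that arm's mRS 0-2 proportion, and two are 2/20 = 10 points. This holds for any patient in the arm. It shows how coarse the proportion is and does not measure an effect of TICI I.

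**Step 5. Outcomes touched.** Infarct volume and 90-day mRS (section 2.5.2) are the ones most tied to recanalisation. The primary outcome, adverse events related to cooling (section 2.5.1), does not depend on final TICI. Spleen volume and blood inflammatory markers bear on the splenic hypothesis whether or not the vessel opens.

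**The case against.** The strongest reply is that the two rules do different jobs. One says which vessels are closed enough to enter, the other which procedures failed outright, and a protocol may choose a lenient threshold for failure. The Introduction also states the working hypothesis for stroke in general: cooling should limit splenic contraction and cytokine release. On that reading a patient at final TICI I is still informative. The primary outcome is safety, efficacy is called preliminary, and the number affected may be zero. Subset definitions can also be left to an analysis plan that is not shown.

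Much of this stands. It limits the consequence to some secondary outcomes and makes the likely dilution modest. It does not remove the mismatch. Two explicit cut-offs in one section disagree on whether grade I is a closed vessel, and the objective itself names recanalisation by thrombectomy. That is not a detail lost in condensing a longer protocol.

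Three stronger readings are not supported:
- A reader might infer that unreperfused patients are kept in the trial. The article does not define the TICI grades. All that can be said is that these patients end at a grade the protocol itself calls occluded.
- A reader might infer that the analysis counts them as recanalised. Section 2.9 names no recanalised analysis set. The comparison is RAH against control.
- A reader might infer that exclusion 2 should simply be widened to TICI 0-I. That would enlarge an exclusion applied after allocation, which is a worse problem than the mismatch.

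**Conclusion.** The concern holds as an inconsistency of definition. Final TICI I is occluded by the entry rule and not unsuccessful by the exclusion rule, and no other criterion settles the matter. The retained patients fall outside the recanalised population named in the objective and efficacy aim.

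The consequence is limited. It falls mainly on infarct volume and 90-day mRS. The primary safety outcome is not affected, and the spleen and blood-marker outcomes largely not. The range of 0 to 4 of 40 patients, and a loss of up to 10% of any reperfusion-related effect, rests on an assumed share of 0% to 10% and on the assumption that these patients have no such benefit. Neither assumption comes from the article. No stated number is wrong. The correction is worth making because it is cheap and the definition may carry into later trials.

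**What to change.** 1. Use one definition: a TICI of 0-I counts as not recanalised, before and after thrombectomy.
2. Reword exclusion 2 so that it no longer removes patients already randomised. Keep every randomised patient in the safety analysis and in the main RAH-versus-control comparison.
3. Use final TICI above I only to define a labelled supplementary recanalised subset for infarct volume and 90-day mRS, and say that this subset corresponds to the question about recanalised patients.
4. State that the subset is selected on a result obtained after allocation and is to be read as exploratory.

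The cost is a short amendment and one supplementary table. Final TICI has to be recorded already to apply exclusion 2 as it stands. The downside is a subset slightly smaller than under the current cut-off, without the full protection of randomisation. The change concerns who is analysed and how, and alters no treatment.

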### Randomization and blindness

2.3

Participants will provide consent and then be randomly assigned to one of the two groups in a 1:1 (*n* = 40) fashion using computer-generated randomization. Patients will be randomized into the groups using opaque randomization envelopes. The nurse who is not blinded will perform RAH and temperature monitoring. After the case observation, neurological function scoring, data collection, and statistical analysis will be performed by the researchers who are blinded to the treatments.

**Figure 2 fig2:**
[figure not shown]
Procedure timeline for protocol. **(A)** Intervention group; **(B)** Control group. MT: mechanical thrombectomy; RAH, remote administration of hypothermia.

**Figure 3 fig3:**
[figure not shown]
Administration of hypothermia (RAH) on the spleen.

Patients in the control group (Sham RAH) will apply packs at room temperature in the left abdomen until 6 h after thrombectomy (Figure 2).

### Outcomes and assessment procedures

2.5

#### Primary outcome (safety)

2.5.1

The primary outcome is safety, defined as any adverse events related to RAH. The main adverse events associated with RAH are focal cold intolerance and abdominal pain. Other adverse events include abdominal skin damage and/or discomfort, such as diarrhea, local frostbite, rash, and chills. All adverse events will be determined independently by trained medical team personnel who are blinded to the randomized groups.

#### Secondary outcomes (efficacy)

2.5.2

(1) Effect of RAH on Spleen: (a) spleen volume measurement: Spleen CT will be performed preoperatively, 24 h and 7 days after MT to determine the change in spleen volume. The area of each layer of the spleen will be calculated by circling the area with the Siemens CT workstation image software, and the overall spleen volume will be calculated by superimposing the layer thicknesses. An ultrasound of the spleen will be performed alternatively if the CT is not done. (b) comparison of blood inflammatory profiles, the changes in inflammatory cells and inflammatory factors (including leukocytes, neutrophils, lymphocytes, tumor necrosis factor, and interleukins 6, 8, and 10, etc.) before, at 24 h and 7 days after MT will be completed. (2) Effect of RAH on Brain: (a) infarct volume (MRI-DWI) between the two groups at 7 days after MT. Infarct volume measurement of cerebral infarcts will be performed by MRI-DWI with a Siemens Syngo workstation. The area of each infarcted layer will be automatically derived by circling the region of interest (ROI) on software of the workstation, and then the overall infarct volume is calculated by superimposing the layer thickness; (b) Intracranial hemorrhage will be classified as symptomatic intracranial hemorrhage based on the following: lethal intracranial hemorrhage and symptomatic intracranial hemorrhage defined as a postoperative CT showing an intracranial hemorrhagic lesion consistent with an NIHSS deterioration score of ≥4 according to the European-Australasian Acute Stroke Study (ECASS II) criteria; (c) comparison of neurological functional independence evaluation at 90-days for functional independence ratio (mRS 0–2 score) and 90-day mortality (mRS 6 score) between RAH and control groups will be determined.

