### Estimation of sample size

2.6

This is a pilot study of the safety of RAH with MT in AIS patients with LVO of anterior circulation. There are no similar clinical studies like this, and thus, no information is available. According to Hertzog (16), 10–20 patients in each group were sufficient to assess the feasibility of a pilot study. Dobkin suggested that a minimum of 15 patients per group would be sufficient to decide whether a larger multicenter trial should be conducted (17). Therefore, we aimed to recruit 20 patients for each group in this study.

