### Statistical analyses

2.9

Data will be entered by persons not involved in the test, using double entry and setting up data range checks. Statistical analysis will be performed using SPSS version 19 (SPSS Inc., Chicago, IL, United States). Categorical variables will be expressed as percentages, and differences will be compared using the chi-square test; continuous variables conforming to normal distribution will be expressed as mean ± standard deviation, and differences will be compared using a *t*-test or ANOVA; continuous variables not all conforming to normal distribution will be expressed as median and upper and lower quartiles, and differences will be compared using rank sum test. Multi-factor linear regression or multi-factor Logistic regression analyses will be performed to control confounding factors according to the data type and outcome. *p* < 0.05 will be considered statistically significant.

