### Limitations

3.5

First, this pilot study will be conducted at a single center with a small sample size, which may limit the generalizability of the findings. Secondly, it is very difficult, if not impossible, to cool the spleen exclusively or to monitor human spleen temperature directly, and the optimal duration and target temperature of RAH remains to be determined. Thirdly, the effect of RAH over the spleen will be inferred indirectly by measuring spleen volume with CT and inflammatory factors in the blood, rather than through direct observation. Lastly, the lack of blinding for the nurse administering the RAH could introduce bias, although this is unlikely to influence the data analysis and final results.

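### The rule allowing ultrasound in place of CT sets no same-modality requirement, so a CT-ultrasound offset can enter a patient's spleen-volume change

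*Protocol article*

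**What the plan says.** Protocol article, section 2.5.2, sets the measurement times and the estimand: "Spleen CT will be performed preoperatively, 24 h and 7 days after MT to determine the change in spleen volume". It fixes a method specific to CT: the spleen is outlined on each slice at the workstation, and "the overall spleen volume will be calculated by superimposing the layer thicknesses". The substitution rule follows at once: "An ultrasound of the spleen will be performed alternatively if the CT is not done".

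Four other places bear on the point:

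- The Introduction gives the mechanism: "the RAH above the spleen is hypothesized to prevent splenic contraction and reduce the release of splenic inflammatory cells and cytokines".
- Section 2.7 (data management) says that missing values will be handled by multiple imputation. It does not say whether a missed CT is imputed or replaced by the ultrasound reading.
- Section 2.9 (statistical analyses) says of normally distributed continuous variables that "differences will be compared using a *t*-test or ANOVA", with a rank sum test otherwise and regression to control confounding. Imaging modality is not named.
- Section 3.5 (limitations) says "the effect of RAH over the spleen will be inferred indirectly by measuring spleen volume with CT and inflammatory factors in the blood". Ultrasound is not mentioned there.

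**The concern.** A change score is interpretable only if both of its measurements estimate the same quantity in the same way. Summed CT slices are one measurement procedure. The ultrasound volume, for which the article states no method, is another. If the two differ systematically, a patient measured by CT at one time and ultrasound at another shows a change equal to the true change plus the offset.

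The direction depends on the order. If ultrasound reads lower, CT followed by ultrasound looks like contraction, and ultrasound followed by CT looks like expansion or hides contraction. Contraction is what the intervention is supposed to prevent. Spleen volume is one of two indirect measures from which the effect on the spleen will be inferred, the other being the blood inflammatory factors. The Conclusion says that the findings will set parameters for later studies, so a distorted mean or standard deviation of change would carry forward.

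**Working it through.** The plan states no figure to reproduce. Section 2.6 takes 20 per group from pilot-study rules of thumb, with no effect size, standard deviation or power. The check is therefore a reading of what the rule permits, followed by an illustration on assumed values.

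**What the rule permits.** There are three times (preoperative, 24 h, 7 days) and two modalities, so 2 x 2 x 2 = 8 modality sequences. Two use one modality throughout. The other six mix CT and ultrasound in at least one change from baseline. In two of those six (ultrasound at baseline only, or CT at baseline only) both changes are mixed. This counts what is allowed, not how often it will happen. Nothing in sections 2.5.2, 2.7, 2.9 or 3.5 rules the six out.

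**Percentage scale (assumptions: no true change; CT at baseline and ultrasound at follow-up; ultrasound reads 10-30% lower).** Each patient who switches shows a false contraction of 10-30%. The spurious between-arm difference is the offset times the difference in switching proportion:

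- 0.10 x 0.20 = 0.02, or 2 points
- 0.30 x 0.20 = 0.06, or 6 points

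The 20-point difference in switching is also assumed. With 20 per arm it means 0.20 x 20 = 4 more switchers in one arm. With equal switching the product is zero.

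**Standardised scale.** Input from the article: 20 per group and p < 0.05 (taken as two-sided). Assumed inputs: q, the share of patients who switch from CT to ultrasound; b, the ultrasound-minus-CT offset; s, the extra ultrasound error. Both b and s are in SDs of true change, and switching is taken as unrelated to true change.

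- Variance of the change in an arm: 1 + q s² + q(1 - q) b²
- Shift of the mean change within an arm: q b
- Between-arm bias: (q_RAH - q_control) b

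Reference with one modality per patient: by the normal approximation, the difference detectable with 80% power is (1.960 + 0.842) x sqrt(2/20) = 0.886 SD.

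*Equal switching, q = 10% to 30%.* Between-arm bias is 0. With b = -1, the mean change in each arm shifts by 0.10 x (-1) = -0.10 to 0.30 x (-1) = -0.30 SD. With b = -1, s = 1 and q = 0.30, the variance is 1 + 0.30 + 0.21 = 1.51, the standard error is sqrt(2 x 1.51/20) = 0.389, and power at 0.886 SD is Φ(0.886/0.389 - 1.960) = about 62%.

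| b, s | Power at 0.886 SD, q = 10% | q = 30% |
|---|---|---|
| 0, 0.5 | 79% | 77% |
| -1, 1 | 73% | 62% |
| -2, 1 | 64% | 48% |

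*Unequal switching, 10% in one arm and 30% in the other.* The bias has size 0.20 x b. For b = -1 and s = 1 the variances are 1.19 and 1.51, the standard error is sqrt(2.70/20) = 0.367, and the bias is 0.20/0.367 = 0.54 standard errors. Type I error is then Φ(-1.416) + Φ(-2.504) = about 8.5%. Over s = 0.5 to 1, it is about 6% for b = -0.5, 8.5-9% for b = -1 and 16-17% for b = -2.

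**The case against.** The article says only that an ultrasound will be done when the CT is not. It does not say that an ultrasound value will be subtracted from a CT value. The sentence could also mean that a patient without CT has ultrasound throughout, in which case no switch occurs. How fallback readings enter the analysis could be settled in a full protocol or analysis plan that is not shown. The limitations section names CT alone, which fits CT as the standard and ultrasound as a fallback. The outcome is secondary in a pilot that promises no power.

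Part of this stands. Mixing modalities is permitted by the lack of a restriction, not prescribed, and the lower power figures breach nothing that the plan promises. But the substitution rule is stated, and it governs data collection. If a patient has CT at one time and only ultrasound at the other, no later analysis plan can recover a same-modality change.

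A reader might also infer more than the documents support:

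- That unstable patients will be the ones to miss CT, or that switching will differ by arm. No section says who will miss a CT, why, or how often. Allocation is randomised, controls receive a sham pack, and data collection is by blinded researchers.
- That the mechanistic result is therefore biased by 2-6 points. The offset, its direction and the imbalance are all assumed, and no expected effect or SD is given to compare them with.
- That this is the trial's main mechanistic outcome. The article lists spleen volume beside the blood inflammatory profile and ranks neither as main.

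**Conclusion.** The point holds as a flaw in a stated measurement rule. The outcome is a within-patient change defined on CT, and the substitution rule allows its two measurements to come from different modalities. Any offset then enters in full for the patients who switch, and only for them; a patient measured by ultrasound throughout is not affected in this way.

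Equal switching does not bias the comparison between arms, but it inflates the variance and shifts the within-arm mean change. Between-arm bias needs unequal switching, for which the documents give no evidence. The size is unknown, because offset, extra error and switching rate are all missing; the figures above show only how it would scale. The primary safety outcome is untouched. The correction is worth making before data collection is complete because it is cheap and cannot be fully made afterwards.

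**What to change.** In section 2.5.2, with a matching line in section 2.9:

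1. Record the imaging modality at every visit.
2. Compute change in spleen volume only between two measurements of the same modality, and never subtract an ultrasound value from a CT value or the reverse.
3. Base the main spleen-volume analysis on CT-to-CT change.
4. Treat a missed CT as missing under the multiple-imputation rule in section 2.7. Ultrasound findings and clinical status may serve as auxiliary information in the imputation model. This also settles which of the two rules applies to a missed CT.
5. Use ultrasound-to-ultrasound change only as a sensitivity analysis, with its volume method stated.
6. Report missed CTs by arm and visit, with reasons.

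The cost is wording, one recorded item per visit, and some observed values. A missed follow-up CT loses one CT-to-CT change; a missed baseline CT loses both. If missed CTs are related to outcome, the result will depend on the imputation assumptions, which is why the reasons need reporting.
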